### Study sample

Local and literature data were evaluated to calculate the sample size [1, 13]. A delirium status prevalence of 20% is estimated in the control group and a decrease in prevalence to 8% in the intervention group is expected. In this way, with a power of 80%, and an alpha of 0.05 bilaterally, 147 patients will be enrolled in each group. If we add to this a 10% loss of follow-up, the overall sample size will be 320 patients (See flow chart in Fig. 1).

**Fig. 1 Fig1:**
[figure not shown]
Patient flow chart

### Interim analysis

The Trial Steering Committee (TSC) was formed with three international experts in the area and will ensure the following aspects:Supervise and guarantee scientific quality.Advise on study protocol, recruitment progress, adherence, follow-up, and data quality.Review the recommendations of the data analysis and monitoring committee.Review the publications in the primary trials.

For the fulfilment of the objectives, the TSC will meet before, in the middle, and at the end of patient recruitment.

### Randomisation

Randomisation will be performed using computer-generated random permuted blocks using a centralised, secure, Web-based randomisation service. A computer will assign blocks of ten for each centre so that in each of the four participating centres, there will be a similar number of patients in each group.

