## Background

Delirium is a clinical condition characterised by acute cognitive impairment, of fluctuating course, generally secondary to an acute pathology, which appears after the interaction between predisposing factors and well-described precipitants. It is a very common condition in older adults, observed in 20–30% of patients hospitalised in a general ward, and up to 80% of those hospitalised in critical care units [1]. Delirium is associated with negative clinical outcomes which include longer hospitalisations, increased direct and indirect costs, functional impairment, greater risk of mortality, increased risk of institutionalisation, and deterioration of long-term cognitive status, among others [1–4].

Subsyndromal delirium is a milder state characterised by the presence of certain delirium symptoms but without meeting full diagnostic criteria thresholds, is also associated with poor posthospitalisation outcomes similar to those associated with delirium [5]. The reported frequency of subsyndromal delirium varies (7–50%) according to the definition applied and the clinical population studied. Its incidence in the general medicine ward is 17% [6].

Delirium in hospitalised older adults is preventable. In multiple randomised clinical trials, non‐pharmacological interventions to prevent delirium (nPPD), shown to reduce its incidence by 30–50% [7]. These interventions include promoting physical activity, facilitating the use of glasses and hearing aids, and providing frequent temporospatial orientation and cognitive stimulation, among others [8, 9]. Despite the high evidence supporting them, nPPD are poorly implemented in hospitals in Chile and around the world for several reasons, including the heavy workload of clinical staff, lack of trained personnel, and in general, the absence of systematic implementation processes [10, 11]. The professional who can more systematically promote cognitive stimulation at the hospital is the occupational therapist. It has been seen that delirium has been prevented in non-ventilated older adults who receive therapy twice a day [9]. However, considering the large number of hospitalised older adults and the number of interventions required for each patient, this alternative is sometimes not very accessible.

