### Participants

The research is developed in four hospital centres of similar complexity located in Santiago, Chile. These are: Hospital Clínico de la Universidad de Chile (HCUCH), Hospital San Juan de Dios, Clínica Las Condes, and Hospital Santiago Oriente [name]. Two are public institutions and two are private institutions. Patients hospitalised in general wards (Geriatric and Internal Medicine Units) and Intermediate Care Units. The units serve older adults admitted for acute pathologies, in the intermediate care unit patients can receive non-invasive ventilation, high-flow nasal cannula, and low doses of vasopressors.

We will include patients 65 years or older, hospitalised less than 48 h prior in a general ward or the intermediate care unit of four participating centres. Patients with full or syndromal delirium (Confusion Assessment Method-[CAM] + or presence of one core element) history of dementia (Alzheimer’s Disease-AD8 greater than 2 points), and non-Spanish speaking patients will be excluded.

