### Analysis and statistical methods

The results will be analysed with the intention to treat. For the descriptive analysis of the variables, we will use the mean (standard deviation), median (25–75 percentile), or proportions as appropriate to the type and distribution of the data.

Analytical Statistics: For the primary outcome, a comparison of proportions between patients who develop delirium and subsyndromal delirium in both groups will be made, using Fisher's exact test, and as a measure of efficacy, an odds ratio with 95% confidence interval will be estimated. If there is any baseline variable that is not matched by the randomisation, efficacy analyses will be conducted using logistic regression with the main variable being the treatment, and the adjustment variables will be those that the randomisation would not have been able to match. Additionally, to compare the effect of the intervention over time, a time-to-event analysis will be performed using the Kaplan-Maier procedure and then the Cox regression model to adjust for baseline variables and the presence of the intervention. For the secondary outcomes, the Fisher's exact test or t-test will be used, as appropriate for the type and distribution of the data. Linear regression or multivariate logistics will also be performed, as appropriate, to evaluate the impact of the intervention, adjusting for the input covariates. A bilateral *p* < 0.05 significance level will be used for all analyses.

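### Unit type and centre are not fixed factors in the primary comparison; adjustment depends on which baseline imbalances are observed

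*Protocol article*

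**What the plan says.** All references are to the protocol article.

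- **Participants.** Patients qualify if "hospitalised less than 48 h prior in a general ward or the intermediate care unit of four participating centres". Of the second setting it says that "in the intermediate care unit patients can receive non-invasive ventilation, high-flow nasal cannula, and low doses of vasopressors".
- **Background.** Delirium is "observed in 20–30% of patients hospitalised in a general ward, and up to 80% of those hospitalised in critical care units". No figure is given for intermediate care.
- **Randomisation.** Permuted blocks are formed within centre: "A computer will assign blocks of ten for each centre so that in each of the four participating centres" the two groups are of similar size. Unit type is not named as a stratum.
- **Study sample.** One control rate covers both settings: "A delirium status prevalence of 20% is estimated in the control group and a decrease in prevalence to 8% in the intervention group is expected".
- **Analysis and statistical methods.** The primary proportions are compared "using Fisher's exact test, and as a measure of efficacy, an odds ratio with 95% confidence interval will be estimated". If a baseline variable turns out not to be balanced, logistic regression on treatment plus the unbalanced variables follows. No threshold for imbalance is given. A Cox model adjusted for baseline variables is also planned, but the variables are not named.

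**The concern.** Unit type is known for every patient at assignment, and the acuity described for intermediate care makes a higher delirium risk there plausible. The design leaves its balance to chance. The analysis takes account of it only if someone judges, after seeing the data, that it is unbalanced. Centre does constrain the randomisation, yet the primary test ignores it.

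Two things are at stake. One is precision: variation between settings stays in the error of the treatment contrast. The other is which estimate carries the conclusion. With no threshold, a difference of 6 to 8 points in unit mix may or may not trigger adjustment, so either the unadjusted or an adjusted odds ratio could become the efficacy result, depending on the data.

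**Working it through.** **1. The plan's own figure.** Inputs from Study sample: 20% versus 8%, 80% power, two-sided alpha 0.05. The pooled-variance formula gives 131 per group; with the continuity correction it gives 147, which matches "with a power of 80%, and an alpha of 0.05 bilaterally, 147 patients will be enrolled in each group". Expected events in 294 evaluable patients: 147 × 0.20 + 147 × 0.08 = 29.4 + 11.8, about 41.

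**2. Assumptions.** The documents give neither the intermediate-care share nor unit-specific risks. Illustrative values: share q = 30%; control risk 40% in intermediate care and 11.4% in wards (0.3 × 40 + 0.7 × 11.4 = 20.0, the planned control rate); relative risk 8/20 = 0.4 in both settings. Intervention risks are then 16% and 4.6%. The gap between settings is 28.6 points in the control arm and 0.4 × 28.6 = 11.4 points in the intervention arm.

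**3. Chance imbalance in unit mix.** SD of the between-arm difference = sqrt(4q(1−q)/294) = sqrt(4 × 0.3 × 0.7/294) = 0.0535, about 5.3 points. The 95% range is ±1.96 × 0.0535, about ±10.5 points. Hypergeometric results with 147 per arm, ignoring the small effect of the centre blocks:

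| Assumed share | SD (points) | P(at least 5 points) | P(at least 10 points) |
|---|---|---|---|
| 10% | 3.5 | 0.12 | 0.005 |
| 20% | 4.7 | 0.24 | 0.04 |
| 30% | 5.4 | 0.37 | 0.06 |
| 40% | 5.7 | 0.41 | 0.07 |
| 50% | 5.8 | 0.35 | 0.10 |

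**4. Effect on the risk difference.** A 10.5-point imbalance puts one arm 5.25 points above the average mix and the other 5.25 below. Shift = 0.0525 × (0.286 + 0.114) = 0.021, or 2.1 points, about 18% of the planned 12. At one SD it is (0.0535/2) × 0.40 = 0.0107, or 1.1 points. The sampling SE of the risk difference is sqrt((0.20 × 0.80 + 0.08 × 0.92)/147) = 0.040, so unit mix accounts for about (1.07/4.0)² = 7% of the variance.

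The risk gap is the least certain input. With relative risk 0.4 the shift is 0.7 × gap × imbalance. For a 10.5-point imbalance and control-arm gaps of 10, 20, 30 and 50 points it is 0.7, 1.5, 2.2 and 3.7 points.

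**5. Operating characteristics.** Simulation of 100,000 trials per setting, 147 per arm, in four scenarios with shares of 15 to 30%, control risks of 10 to 17% in wards and 32 to 48% in intermediate care, and a common odds ratio set so that the overall rates are 20% and 8%. A pooled z-test stood in for Fisher's test. The CMH test was stratified by unit only; centre was not simulated.

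| Randomisation | Test | Power | Type I error |
|---|---|---|---|
| Not stratified by unit | unadjusted | about 0.86 | 0.05 |
| Not stratified by unit | CMH by unit | 0.860–0.891 | about 0.05 |
| Stratified by unit | unadjusted | 0.862–0.873 | 0.034–0.046 |
| Stratified by unit | CMH by unit | 0.863–0.893 | about 0.05 |

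Using unit type in the analysis brings nearly all the gain. Stratifying while keeping the unadjusted test makes that test conservative.

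**6. The two odds ratios differ.** At 8% versus 20% the unadjusted odds ratio is (0.08/0.92)/(0.20/0.80) = 0.348. The within-unit odds ratios that produce those overall rates in the four scenarios are 0.306 to 0.342. Adjusting or not changes the quantity estimated, even with perfect balance, so the choice should not wait for the data.

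**The case against.** The strongest defence has four parts.

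- **The risk gap is not documented.** A reader might infer from Background that delirium risk differs sharply between the two settings. The text does not support that: the upper figure is for critical care, and the trial enrols from intermediate care. Background also describes hospitalised patients in general, whereas the trial excludes patients with delirium or a core delirium feature at entry and those with AD8 above 2. A higher risk in intermediate care is plausible; its size is unknown. Nor does the article say that ability to use the tablet differs by unit. This part stands.
- **The plan already provides for imbalance.** The conditional logistic regression is written for this case, and APACHE II, SOFA and Charlson scores are collected as measures of illness. That lessens the harm. It does not remove it, because the rule selects covariates from the data and names neither unit type nor centre.
- **The consequence is small.** This stands. A reader might apply the 28.6-point control gap to both arms and get 10.5% × 28.6 = 3.0 points, a quarter of the planned effect. That holds only if treatment does nothing; under the planned effect the shift is 2.1 points. Ordinary chance imbalance is already covered by the confidence interval.
- **Centre is a sensible stratum, and covariate lists belong in an SAP.** Two centres are public and two private, and one has previous research experience with the prevention programme and the software, so blocking by centre is well motivated. Silence on covariates would indeed be no finding. Here, however, the article itself lays down an unadjusted test with an imbalance-triggered rule.

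**Conclusion.** The point holds as a modest one about the analysis. Two settings of different acuity are enrolled. Neither unit type nor centre is a fixed factor in the primary comparison, and adjustment is decided by observed imbalance.

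The allocation is not invalid or biased: type I error of the unadjusted test stays at 0.05 in the simulations. The simulations did not cover a conclusion drawn from whichever odds ratio the imbalance rule selects. The precision loss is small, with power of about 0.86 unadjusted against 0.860–0.891 when unit type is used. The illustrative shift of about 2 points in the risk difference comes from an imbalance at the edge of its 95% range and rests on the assumed share, unit risks and relative risk. The main reason to act is that the primary odds ratio should be defined before the data are seen, which costs almost nothing.

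**What to change.** In Analysis and statistical methods, replace the imbalance-triggered adjustment for the primary outcome with one pre-specified comparison adjusted for centre and for unit type at assignment. Logistic regression with both as fixed factors, or a CMH test stratified by them, would serve. Fix it before unblinding, say that its odds ratio is the primary estimate, and report event rates by arm within unit type. Unit type should be the unit at assignment, so that later transfers do not alter it.

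If randomisation has not started, unit type may also be made a stratum within centre: 4 × 2 = 8 lists instead of 4. This is optional, and should be done only together with the adjusted analysis.

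The cost is a few lines of text, with no extra patients and no extra data beyond recording unit type at assignment. The optional strata add a list set-up change and slightly more incomplete blocks. The required sample size does not change.

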### Management, implementation and masking

All the centres have geriatric units and a rehabilitation team that includes a physiatrist, kinesiologist, occupational therapist, and speech therapist. All centres have delirium prevention protocols, one of them with formal research in the implementation of nPPD and use of the software (pilot studies) [12, 13]. Each centre has a specific coordinator and implementing staff. All care providers will take an online course in non-pharmacological management of delirium that will be led by a multidisciplinary research team (physicians, nurses, occupational therapists, and engineers). This will be conducted before recruitment to achieve a homogeneous standard of treatment. In addition, they will participate in telematic meetings to disseminate information, get feedback to increase adherence.

When the patient signs the informed consent, the recruiter will give notice to an independent statistician who will make the random assignment and inform the tablet coordinator via text message, the coordinate will be in charge of installing or not the PREVEDEL software in the tablet according to the assigned group. This person will not have any contact with the patients. A healthcare professional (doctor or occupational therapist) will deliver the tablet and train the patient on how to use it.

The enrollers, evaluators, and healthcare personnel (nurses, physical therapists, physicians, occupational therapists) will be blind to the group assignments. Both groups will receive a tablet of the same dimensions and with the same basic applications. However, blinding the patient is not possible, as when exploring the tablet, he or she will recognise whether or not it has the PREVEDEL program included. To reduce this bias, the staff who delivers the tablet to the patients encourages both groups to use its different basic applications, that they access the internet, and that any questions they may have about its use should be addressed to the tablet coordinator so that the evaluators or healthcare personnel remain blinded.

The time between the assignment and delivery of the tablet will between 4–12 h in all participating centres. This variable will be measured for later analysis.

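### A single published block size of ten in every centre lets up to one allocation in six be foreseen, if recruiting staff learn all earlier allocations at their centre

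*Protocol article*

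**What the plan says.** The Randomisation section specifies "computer-generated random permuted blocks using a centralised, secure, Web-based randomisation service". It then fixes the size: "A computer will assign blocks of ten for each centre". The stated purpose is that "in each of the four participating centres, there will be a similar number of patients in each group", which implies 1:1 allocation, five and five per block.

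Management, implementation and masking gives the safeguards. Assignment follows consent: "When the patient signs the informed consent, the recruiter will give notice to an independent statistician who will make the random assignment". Recruiters, assessors and healthcare staff, with physicians, nurses and occupational therapists named, "will be blind to the group assignments".

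The document also describes ways in which an arm can become known at a site:

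- In the masking section: "blinding the patient is not possible, as when exploring the tablet, he or she will recognise whether or not it has the PREVEDEL program".
- In the same section: "A healthcare professional (doctor or occupational therapist) will deliver the tablet and train the patient on how to use it". Under Interventions, the training takes 10–15 minutes and the same person returns the next day to deal with problems.
- The description of the configuration module, also under Interventions, says that healthcare personnel, nurses above all, can tailor PREVEDEL to the patient. Only the experimental arm has PREVEDEL to tailor.

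**The concern.** Central assignment after consent hides the list. It does not stop anyone who knows the block size and the earlier arms from deducing what is left in the block: once five patients in a block have gone to one arm, the rest must go to the other. The block size is public and the same everywhere, so the only remaining protection is that recruiters do not learn past arms. The document asserts this, but several of its own procedures work against it.

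Selection at recruitment is at stake. A recruiter who can foresee the next arm could delay or withhold an approach to a particular patient. There is some room for this: a 48-hour window after admission, and exclusions that depend on a judged CAM element and an AD8 score (Participants). The planned logistic regression adjusts for baseline variables that turn out unbalanced. It cannot be relied on to remove selection on characteristics that were not measured.

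**Working it through.** The plan gives no predictability figure to reproduce.

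**Inputs.** Block size 10 within centre and 1:1 allocation (Randomisation); 320 patients (Study sample). Assumptions: all blocks are filled, and the recruiter knows where each block starts. The simulations in step 5 also assume 80 patients per centre; the document gives no split by centre.

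**1. Upper bound: every earlier arm known.** The next allocation is certain once one arm has used its five places. After k allocations in the block, the probability of this is 2·C(k,5)/C(10,5), with C(10,5) = 252.

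| Position in block | k | Probability that the allocation is certain |
|---|---|---|
| 1 to 5 | 0 to 4 | 0 |
| 6 | 5 | 2/252 = 0.8% |
| 7 | 6 | 12/252 = 4.8% |
| 8 | 7 | 42/252 = 16.7% |
| 9 | 8 | 112/252 = 44.4% |
| 10 | 9 | 252/252 = 100% |

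The sum is 420/252 = 1.67 per block of ten, or 16.7%. The closed form 1/(m+1) with m = 5 gives the same 1/6, as does enumeration of all 252 sequences. Over 320 patients, 320/6 = 53.3.

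**2. Best guess with full knowledge.** The expected proportion of correct guesses is (m + (4^m/C(2m,m) − 1)/2)/(2m) = (5 + (1024/252 − 1)/2)/10 = (5 + 1.53)/10 = 65.3%.

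**3. Partial knowledge.** Suppose each earlier arm is known independently with probability q (an assumed value). Certainty then needs all five members of the exhausted arm to be known, so the share is (1/6)·q^5.

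- q = 0.9: 0.1667 × 0.590 = 9.8%
- q = 0.75: 0.1667 × 0.237 = 4.0%
- q = 0.5: 0.1667 × 0.031 = 0.5%
- q = 0: 0

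A simulation of 60,000 blocks at each value gave 9.8%, 3.9%, 0.5% and 0.

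**4. Only the latest arm unknown.** This could arise because the tablet arrives 4–12 hours after assignment. Each probability in the table then moves one place later and the last drops out: (2 + 12 + 42 + 112)/252 = 0.667 per block, or 6.7%.

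**5. Varying sizes.** Simulated centres of 80 patients, with an observer who knows all past arms and the set of sizes but not their order:

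| Block sizes | Certain | Best guess correct |
|---|---|---|
| Fixed 10 | 16.6–16.7% | 65% |
| Random 8, 10, 12 | 1.3–1.4% | 65% |
| Random 6, 8, 10 | 1.6% | 66% |
| Random 4, 6, 8 | 2.2–2.3% | 68% |

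With 8, 10 and 12, the certain allocations number about 4 of 320 (320 × 0.013 = 4.2).

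**6. Imbalance.** The largest within-centre difference is half the largest block: 10/2 = 5 now, 12/2 = 6 with 8, 10 and 12.

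**The case against.** The plan has real safeguards: consent before assignment, an independent statistician, tablets of the same size with the same basic applications, questions routed away from assessors and ward staff, and recruiters declared blind. If recruiters are blind in practice, nothing is predictable. The document does not say that the person who delivers the tablet also recruits or passes anything on. Ten is also one of the safer fixed sizes: by the same formula, a fixed block of 4 makes one allocation in three certain and a block of 6 one in four. The gain from varying the size is limited to certainty, because guessing accuracy hardly moves. All of this stands, and it is why the figure has to be an upper bound.

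A reader might go further in three ways that the document does not support.

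- That the design as written makes one allocation in six predictable. This needs complete knowledge of earlier arms and of the block boundaries, which the document does not show recruiters to have.
- That the PREVEDEL screen is on view to recruiters all day. The tablet is with the patient from 9:00 to 20:00, but the advice is for three sessions of at least ten minutes, and nothing says where recruiters work.
- That the block size also exposes the CAM assessments. An assessor who sees the tablet or hears from the patient learns the arm directly, whatever the block size.

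The objection does not restore the blinding that it relies on. Occupational therapists and physicians are listed as blind, yet one or the other trains the patient on the device; nurses are listed as blind, yet may configure software that only one arm has.

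**Conclusion.** The point holds as a conditional weakness in concealment. The block size is fixed, public and identical in all centres, and the described workflow gives site staff ways to learn past arms. The share of allocations foreseeable with certainty before consent lies between zero (recruiters fully blind) and 16.7%, about 53 of 320 (every earlier arm and each block start known). The document does not allow the true position in that range to be fixed, and it does not show that selection would occur. The improvement is nearly free and worth making in a trial whose patients know their arm. It concerns selection at recruitment only.

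**What to change.** For blocks not yet generated, replace the fixed size in the Randomisation section with wording such as: *Permuted blocks of randomly varying size (for example 8, 10 and 12) will be used within each centre; the sizes and their order will be known only to the independent statistician and not disclosed to site staff.* Avoid small sets such as 4, 6 and 8, which raise best-guess accuracy to about 68%.

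The cost is a new list for the remaining blocks, one line of text, and a maximum within-centre imbalance of 6 instead of 5. The gain is that worst-case certain allocations fall from 16.7% to about 1.3%; best-guess accuracy stays at about 65%.

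Separately, reconcile the statements in Interventions and in Management, implementation and masking on who handles, configures and explains the tablet with the list of those declared blind. The coordinator who installs the software is said to have no patient contact, yet patients' questions are directed to the tablet coordinator; this needs reconciling too. Varying the block size does not settle any of these.
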